#### 8.4.5 Reporting of Safety Events by the Sponsor

It is the responsibility of the Sponsor/representative to communicate any information regarding study subject's safety and/or affecting whatsoever the study's benefit/risk ratio to the Spanish Agency of Medicines and Sanitary Products (AEMPS) and the EC within 15 calendar days of learning the event.

The Sponsor will keep a record of all AEs reported by Investigators. These records will be submitted to regulatory authorities when requested.

##### 1.1.1.1 Annual Safety Report (DSUR)

The Sponsor/ representative will prepare and timely submit annual safety reports to the regulatory authorities, i.e., the Spanish Agency of Medicines and Sanitary Products (AEMPS) and CE for the whole study's duration. Safety reports content and submission must follow the ICH E2F guidelines, and pertinent regulations.

##### 1.1.1.2 Safety Report to Study Investigator

It is the responsibility of the Sponsor to communicate any information regarding study subject's safety to the Investigator as soon as possible.

Information regarding study's SUSARs information will be sent to the Investigator annually through a line listing, together with a summary of the data analysis. The Investigator will also be informed throughout the study about all aspects related to safety, including amendments to the protocol due to safety reasons.

#### 8.4.6 Expedited Reporting of SUSARs by the Sponsor

It is the responsibility of the Sponsor/ representative to communicate any SUSAR occurring from the time of subject's inclusion in the study through the complete duration of the study (7 months) to the regulatory authorities, i.e., the Spanish Agency of Medicines and Sanitary Products (AEMPS) through EudraVigilance, and to the competent bodies of the Autonomous Communities in whose territory the study is being conducted.

According to AEMPS regulations (section 8 of the AEMPS' Instructions for the Conduction of Clinical Trials), it is not necessary for the Sponsor to communicate study SUSARs to the EC.

As defined in section 8.4.1, a SUSAR is any adverse event meeting the following three criteria:

- Serious,

- Unexpected
- Associated to the administration of the study vaccine.

The study Sponsor will report the adverse experience to MSD, the study funder, as specified in the study agreement signed with MSD.

The latest deadline for SUSARs reporting will be 15 calendar days from the time the Sponsor becomes aware of the event. For SUSARs causing death or being life-threatening for the subject, the latest deadline will be 7 calendar days. When possible, complete information on the event will be provided in the following 8 days.

Information on adverse events that are not serious or unexpected and on those considered unrelated to the study vaccine will be collected in tabular form at the end of the study.

The Sponsor/representative will keep a record of all AEs reported by Investigators. These records will be submitted to the Spanish Regulatory Agency when requested.

#### 8.4.7 Follow-Up of Adverse Events

It is the responsibility of the Investigator to follow up SAEs, and other reportable safety events, and to report information related to the events until it has subsided, returned to baseline, can be attributed to products other than the study vaccine or to factors unrelated to the conduct of the study, it is unlikely to obtain additional information, or in case of permanent impairment, until the condition stabilizes.

#### 8.4.8 Exposure During Pregnancy and Breastfeeding

Although not considered an adverse event, it is the responsibility of the Investigator to report immediately to the Sponsor/ representative any pregnancy or suspected pregnancy (including positive pregnancy tests regardless of age) occurring throughout the study and within 28 days after the end of the treatment.

According to Gardasil-9™ Summary of Product Characteristics, a large amount of data on pregnant women (more than 1000 pregnancy outcomes) indicates no malformative nor foeto/neonatal toxicity of 9vHPV. Animal studies do not indicate reproductive toxicity. However, these data are considered insufficient to recommend use of 9vHPV during pregnancy. Therefore, a specific selection criterion has been defined, excluding candidates who are pregnant or plan to be during the study (section 5.2).

Any pregnancy occurring after subject's inclusion in the study and exposure to any number of vaccine doses will be followed up to delivery for possible adverse events related to malformation or foeto/neonatal toxicity.

The Investigator will follow the female subject until completion of the pregnancy, and must notify UICEC-IDIBELL immediately about the outcome (either normal or abnormal outcome) of the pregnancy (including spontaneous abortion or voluntary termination, details of birth and the presence or absence of any birth defects, congenital abnormalities or maternal and new-born complications) by email or fax, and by sending a completed Pregnancy Notification Form.

If the outcome of the pregnancy was abnormal (e.g., therapeutic abortion), the Investigator should report the abnormal outcome as an AE. If the abnormal outcome meets any of the

serious criteria, it must be reported as an SAE to UICEC within 24 hours of the Investigator's knowledge of the event using the SAE Notification Form.

According to Gardasil-9™ Summary of Product Characteristics, it is safe to use 9vHPV during breastfeeding.

## 8.5 VISIT REQUIREMENTS

### 8.5.1 Screening Visit: Day 1/ Visit 1.

Inclusion/exclusion criteria in sections 5.1 and 5.2 specifies restrictions and requirements for Day 1. Signing of Informed Consent, screening of candidates and vaccination with the first dose of Gardasil-9™ will be performed on Day 1. See Schedule of Activities in section 1.2.2 for the specific study procedures on Day 1.

### 8.5.2 Vaccination Visits: Day 1, Month 2 and Month 6.

Prerequisites for the three vaccination visits are the following:

- The subject has not had a fever (defined as temperature  $\geq 37.8^{\circ}\text{C}$ ) within the 24-hour period prior.
- Has not received a non-study inactivated or recombinant vaccine within 14 days prior to any study vaccination visit or a non-study live vaccine within 21 days prior to any study vaccination visit.

If the subject does not meet the requirements listed above, the study visit (including sample collection and study vaccination) should be re-scheduled.

### 8.5.3 Cervical, Anal, Urine, Vulvar and Oral Sample Collection Visits: Day 1, Month 2, Month 6 and Month 7.

On visits when cervical, anal, urine, vulvar and oral samples will be collected from the study subject, she must not have engaged in sexual activity within the 48 hours prior. See section 5.2.4 for definition of sexual activity.

The purpose of this restriction is to avoid HPV type-specific contamination of collected specimens due to sexual partner's fluids deposition.

If the subject does not meet this requirement, the study visit (including sample collection and study vaccination) should be re-scheduled.

The subject should not have her period to collect the samples. If the subject does not meet this requirement, the study visit should be re-scheduled.

### 8.5.4 Blood Sample Collection Visits: Day 1, Month 2, Month 6 and Month 7.

As described in the exclusion criteria list (see section 5.2.2), for candidate enrolment in the study she must not have received within the 3 months prior to the Day 1 visit, any immune globulin product or blood-derived product other than IVIG.

This requirement should be fulfilled throughout the whole duration of the study, to avoid possible interactions between immunoglobulin products and study vaccine or study antibody determination.

## 9 STATISTICAL ANALYSIS PLAN

### 9.1 Study Objectives, Endpoints and Data Analysis

#### 9.1.1 Primary Objective

##### 9.1.1.1 Objective 1

To demonstrate that vaccination with a 3-dose regimen of 9vHPV will reduce viral infectivity in cervical, anal, urine, vulvar and oral samples from HPV 16/18/16+18-positive women.

##### 9.1.1.1.1 *Endpoint*

In-vitro infectivity evaluation (by expression of E1+E4 HPV biomarker in HaCaT keratinocytes) of cervical, anal, urine, vulvar and oral samples collected before and after 9vHPV vaccination in a 3-dose regimen.

##### 9.1.1.1.2 *Inclusion in the analysis population*

The below criteria will be followed to include cases in the analysis population:

Before vaccination (Visit 1):

- HPV16/18/16+18 positive DNA detection and genotyping (using Anyplex HPV28) in collected cervical, anal, urine, vulvar and oral samples.
- HPV16/18 positive virion detection (using ELISA, electronic microscopy) in collected cervical, anal, urine, vulvar and oral samples.

Therefore, cases showing:

- negative HPV16/18 DNA test and/or
- absence of HPV16/18 viral particles,

will not be included in the analysis population.

After vaccination (Visits 2 to 4, Months 2, 6 and 7):

- HPV16/18/16+18 positive DNA detection and genotyping (using Anyplex HPV28) in collected cervical, anal, urine, vulvar and oral samples.
- HPV16/18 positive virion detection (using ELISA, electronic microscopy) in collected cervical, anal, urine, vulvar and oral samples.
- Positive detection of exudated HPV 6/11/16/18/31/33/45/52/58 L1 antibodies in collected cervical, anal, urine, vulvar and oral samples.
- Positive detection/titration of HPV 6/11/16/18/31/33/45/52/58 L1 antibodies in collected serum samples (positive seroconversion).

Therefore, cases showing:

- negative HPV16/18 DNA test and/or
- absence of HPV16/18 viral particles and/or

- absence of exudated HPV L1 antibodies and/or
- absence of positive seroconversion,

will not be included in the analysis population.

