| 
1) Primary Objective. To demonstrate that vaccination with a 3-dose regimen of 9vHPV will reduce viral infectivity in cervical, anal, urine, vulvar and oral samples from HPV 16/18/16+18-positive women.
 
Hypothesis. 9vHPV promotes the production and exudation of anti-HPV antibodies, which neutralize new HPV16/18 virions and reduce the infective capacity of body fluids in HPV-positive women and the transmission of HPV infection.
 | 
 
● In-vitro infectivity evaluation (by expression of E1^E4 HPV biomarker in HaCaT keratinocytes) of cervical, anal, urine, vulvar and oral samples collected before and after 9vHPV vaccination.
 
● Detection of HPV 6/11/16/18/31/33/45/52/58 L1 antibodies in cervical, anal, urine, vulvar and oral samples collected before and after 9vHPV vaccination, using             
 
– ELISA for types 16 and 18 in samples from RIFT-HPV 1 and 2 study cohorts,
 
– cLIA for all 9vHPV-covered types in samples from RIFT-HPV 1 study cohort.
 
 
This endpoint will allow associating the reduction in viral infectivity with the presence of neutralizing antibodies.
 
 
● HPV16/18 virion detection (using ELISA, electronic microscopy) and HPV DNA
 
 |

|                                                                                                                                                                                                                                                                                                                                                                                                                                                                                                                                           |                                                                                                                                                                                                                                                                                                                                                                                                                  |

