During Visit 1, eligibility criteria defined in section [5](#) will be reviewed with subjects after they read the Subject's Information Sheet and sign the Informed Consent Form (annex [11.2](#)). Those subjects complying with inclusion and exclusion criteria will be enrolled in the study and included in RIFT-HPV 1 or 2 study cohorts according to baseline characteristics.

All enrolled subjects will complete the specified procedures in 4 study visits: Visit 1/Day 1, Visit 2/Month 2, Visit 3/Month 6, and Visit 4/Month 7. Study procedures and time windows for each visit are summarized in the Schedule of Activities (section [1.2.2](#)).

9vHPV vaccine will be administered in Visits 1, 2 and 3 by a qualified health professional (Study nurse/Sub-Investigator).

There is no control group in this study: all subjects signing the Informed Consent Form will receive 9vHPV vaccination in a three-dose regimen as per protocol (section [8.1.9](#)) and therapeutic indication.

All enrolled subjects will follow the study procedures summarized below as per protocol (section [1.2.2](#)):

- Pregnancy test on a urine sample in Visits 1, 2, 3 and 4 before receiving any vaccine or collecting any sample.
- Completion of a questionnaire in Visits 1 and 4.
- Cervical, vulvar and anal sample collection by the study Investigator, and oral, urine and blood sample collection by the study nurse. All samples will be collected in Visits 1, 2 and 3 before receiving 9vHPV vaccination, and in Visit 4.
- Intramuscular administration of 9vHPV in a three-dose regimen in Visits 1, 2 and 3.

The following study laboratory procedures will be applied to samples obtained from study subjects:

- Assessment of HPV infectivity. Analysis of E1+E4 HPV biomarker expression in HaCaT keratinocytes in-vitro after exposure to cervical, anal, urine, vulvar or oral samples from all study subjects.
- Assessment of HPV positivity. Detection of HPV16 and 18 in cervical, anal, urine, vulvar and oral samples from all study subjects, using ELISA/electron microscopy to detect HPV virions, and HPV test/genotyping (Anyplex HPV28) to detect HPV DNA.
- Assessment of HPV immunogenicity. Detection and titration of anti-HPV L1 antibodies in serum, cervical, anal, urine, vulvar and oral samples from all study subjects, using ELISA for types 16 and 18 in samples from RIFT-HPV 1 and 2 study cohorts, or cLIA for all 9vHPV-covered types in samples from RIFT-HPV 1 study cohort.

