#### **8.2.2.4 HPV16/18 virion detection and antibody titration (ELISA, electronic microscopy)**

Enzyme-linked immunosorbent assays (ELISA) will be performed as primary method to detect and quantify HPV16/18 antibodies in serum samples of RIFT-HPV Cohort 1 and RIFT-HPV Cohort 2, and HPV16/18 virions in cervical, anal, urine, vulvar and oral samples from the study subjects. The purpose of the test is to distinguish reduction of infectivity due to 9vHPV vaccination from non-productive HPV infections.

A sandwich ELISA assay will be used to detect the major capsid protein L1 of HPV 16/18 present in serum and in exudates of productive infections. Samples will be centrifuged for 20 minutes at 3000 rpm and supernatants recovered and added to microtiter plates with wells coated with anti-HPV 16/18 L1 capture antibodies. Samples and controls will be incubated for 20 minutes to let the antigens bind to the capture antibodies and afterwards a washing step will be done for removing unbound substances. A reporter antibody conjugated with HRP enzyme will be added for antigen detection and incubated for 1 hour, followed by a washing step to remove the excess of reporter antibody. Finally, a chromogenic HRP substrate will be added, and optical density measured for indirect quantification of bound virions.

Productive infections will be detected through the identification of new viral particles by electron microscopy (EM) in cervical samples and HPV positive oral and anal samples as previously described. EM experiments will be performed using the scientific platform of the University of Barcelona (UB). The EM will offer a direct measure of viral particles to confirm the virus production, while the ELISA test will offer a faster and more sensitive measurement especially in samples in which a low viral load is expected (oral samples).

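### The primary analysis set excludes women without an antibody response after vaccination, so the result describes responders; its nine-type antibody criterion also lacks an all-or-any rule

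*Protocol*

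**What the plan says.** Section 9.1.1.1.2 of the Protocol fixes who enters the primary analysis. At Visit 1 a case needs HPV16/18 DNA and HPV16/18 virions. A second block, which opens "After vaccination (Visits 2 to 4, Months 2, 6 and 7", asks for both again and adds two antibody conditions: "Positive detection of exudated HPV 6/11/16/18/31/33/45/52/58 L1 antibodies in collected cervical, anal, urine, vulvar and oral samples", and the same nine-type list in serum. The exclusion list that follows removes cases with a negative DNA test, "absence of HPV16/18 viral particles and/or" "absence of exudated HPV L1 antibodies and/or" "absence of positive seroconversion".

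Section 9.1.1.2 then compares Visit 1 with Visit 4 by a Wilcoxon signed rank test, with cervical samples analysed jointly and by cohort and the other four sites pooled over both cohorts. The one named sensitivity analysis is restricted to women who were seronegative before vaccination. Section 9.1.3 adds only unspecified analyses based on the questionnaire.

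On the assays, section 4.1 says antibodies are measured "using ELISA for types 16 and 18 in samples from RIFT-HPV 1 and 2 study cohorts, or cLIA for all 9vHPV-covered types" in RIFT-HPV 1. The Schedule of Activities (1.2.2) agrees: the seven other types are run in RIFT-HPV 1 only. The synopsis says of the mucosal antibody endpoint: "This endpoint will allow associating the reduction in viral infectivity with the presence of neutralizing antibodies".

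**The concern.** Mucosal antibody and seroconversion are the means by which the vaccine is supposed to act. Making them conditions of entry selects women on the vaccine's effect. Those in whom no neutralisation is expected are removed, and the result in the remainder would be reported as the effect of vaccination. The study has one arm and no control group, so nothing else in the design would reveal the selection. Such women are foreseeable: section 9.1.2.1.2 expects 10% not to seroconvert, and section 5.1 admits women with HIV, transplant immunosuppression or other immunosuppressive conditions. The four reasons behind the 40% loss allowance in section 9.2.1 do not include missing antibody.

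The antibody criterion is also not operational. It names types that one of the two cohorts is never tested for, and does not say whether all or any must be positive.

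**Working it through.** **1. Whom the rule removes.** Objective (9.1.1.1): vaccination reduces infectivity in HPV16/18-positive women. Rule (9.1.1.1.2): only cases with serum and mucosal antibody after vaccination count. Definition (9.1.4): a negative serum result may reflect failure of the vaccine to trigger a response. Together these mean that immunological vaccine failures leave the primary set by rule. The named sensitivity analysis narrows the set further and restores nobody.

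**2. Size of the selection.** Inputs: seroconversion share s = 0.90 (9.1.2.1.2); target reductions 25% cervical (9.2.1) and 35% anal (9.2.2). Assumption not in the documents: reduction in non-responders F = 0.

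Overall reduction = s × R + (1 − s) × F, where R is the reduction in the retained set.

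- Cervical: 0.90 × 25% + 0.10 × 0 = 22.5%; ratio 25 / 22.5 = 1.11.
- Anal: 0.90 × 35% = 31.5%; the same ratio.
- In reverse, a true overall 25% would appear as 25% / 0.90 = 27.8%.

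The 90% refers to serum. The protocol gives no expected share for antibody at any mucosal site, so the share removed there is unknown. If it were anywhere from 5% to 30% (assumption), a retained-set 25% would be 0.95 × 25% = 23.75% down to 0.70 × 25% = 17.5% overall. If non-responders did show some reduction, the gap would be smaller.

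**3. The nine-type criterion.** The plan's anal head count (9.2.2) reproduces: 0.60 × 30 = 18.0 from RIFT-HPV 2 and 0.28 × 39 = 10.9 from RIFT-HPV 1, together 28.9 against the stated 18 + 10 = 28. The power basis for 28 (and for 39) cannot be reproduced, because no standard deviation or baseline rate is given.

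- *All nine required.* Nobody in RIFT-HPV 2 can qualify, since seven types are not assayed. The anal set falls from 28 to 28 − 18 = 10, or about 11 before rounding. To illustrate with a paired normal approximation, 80% power at 28 implies a standardised effect of (1.96 + 0.842) / √28 = 0.529. Power at n is then Φ(0.529 × √n − 1.96), which is about 39% at n = 10 and 42% at n = 11.
- *Any one type sufficient.* RIFT-HPV 2 stays and this loss is zero. But a woman infected with type 16 could qualify on antibody to type 6, and RIFT-HPV 1 has nine ways to qualify against two in RIFT-HPV 2, in cohorts that are pooled.

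**4. Visits and types.** The conditions cover Visits 2 to 4, but the primary test uses only Visits 1 and 4. The text does not say whether a negative result at Month 2 removes a woman from a comparison that does not use Month 2. Nor does it require the same type (16 or 18) before and after, although section 9.1.4 defines persistence by the same genotype.

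**The case against.** The study is presented as a proof of concept for neutralisation by antibody, and a set in which antibody is present is a fair place to look for that mechanism. This stands as a reason to keep the rule as a supporting analysis. It does not make that set an answer to the primary objective as worded.

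Four stronger readings are tempting, and the documents do not support them.

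- *That RIFT-HPV 2 cannot meet the criterion.* This is true only if all nine types are required. The text does not say so, the exclusion line refers to L1 antibodies without listing types, and section 9.1.1.2 plainly intends the cohort to be analysed.
- *That the virion condition also removes vaccine failures.* It does not. Section 2.1 says the vaccine affects neither existing infection nor production of new particles, and section 8.2.2.4 gives the purpose of virion detection as separating neutralisation from non-productive infection. Without controls, that is a legitimate filter. The ELISA does rely on "wells coated with anti-HPV 16/18 L1 capture antibodies", and section 2.2.4 suggests that vaccine antibody could coat the capsid, so well-neutralised samples might read as negative. That is inference: no interference is reported, and electron microscopy is also accepted, though section 8.2.2.4 does not list it for urine or vulvar samples. Such masking would bias the estimate downwards, against the antibody selection.
- *That infectivity can no longer be related to antibody.* The loss is partial. Mucosal antibody is reported only as present or absent, so that contrast disappears in the primary set, but serum antibody is quantitative.
- *That only about half the women survive the rule.* With 95% success on each of four criteria at three visits, 0.95^12 = 54%; at one visit, 0.95^4 = 81%. Both need independence and success rates that the protocol does not give.

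**Conclusion.** The concern holds for the antibody and seroconversion conditions. They select the primary set on the vaccine's own effect, no planned analysis undoes this, and the result describes responders. On the protocol's 90% figure, and assuming no reduction in failures, the overstatement is about 1.1 times (25% against 22.5%). A reader might infer a much larger distortion, such as 1.7 times at 60% antibody positivity, but that 60% is not in the documents.

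The nine-type criterion is undefined rather than impossible. One reading contradicts the pooling in section 9.1.1.2 and would cut the planned anal set from 28 to about 10; the other admits antibody irrelevant to the infecting type. The power figures given for the first reading are illustrative. The virion condition is a trade-off to report openly, not an error to delete.

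**What to change.** Rewrite section 9.1.1.1.2, which section 9.1.2.2.1 also applies to the one-dose and two-dose comparisons:

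- Define the primary set per anatomical site: HPV16/18 DNA and virions at Visit 1, paired Visit 1 and Visit 4 samples, and the same type (16 or 18) still DNA-positive at Visit 4.
- Remove the post-vaccination antibody and seroconversion conditions from the primary set.
- Keep the Visit 4 virion condition as the filter for non-productive infection, and report the analysis with and without it because antibody may interfere with the L1-capture ELISA.
- Apply each criterion only at the visit being compared.
- Use the 16/18 ELISA antibody result matched to the woman's type, the assay run in both cohorts, as an explanatory variable. This also settles the all-or-any question.
- Keep the present antibody-positive rule as a labelled sensitivity analysis, with its type requirement stated.

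The cost is a wording amendment, with no new samples or assays. The estimated reduction may be smaller once non-responders are included. The version without the virion condition could move the other way, since it admits women who have stopped producing particles, so both results should be shown together.
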